#### Subsidiary aims

Subsidiary aims include the following:Levels of student and staff exposure to Sources of Strength whole-school messaging will also be explored, including a *social network* analysis in a subset of intervention schools to determine whether peer leader messaging increases the density of positive social ties across students and increases positive connections to adults, particularly among isolated students. The social network investigation will also test engagement with social media messages posted by peer leaders at the intervention schools, accounting for both virtual and self-reported social networks within each school.Data collected from the study will also be used to test models of *suicide risk*, including the Interpersonal Theory of Suicidal Behavior [14, 15] and the relationship between positive future thinking and suicide risk [17]. These models will explore a range of potential risk and protective factors, such as perceived burdensomeness, thwarted belongingness, acquired capability for suicide, entrapment, self-harm, depressive and anxiety symptoms, personality, and risk-taking. Analyses will be conducted cross-sectionally and prospectively.Lastly, *predictors and mediators* of intervention effects and intervention engagement will also be explored, including demographic characteristics, suicide stigma, suicide literacy, suicidal ideation, depressive symptoms, bullying, school inclusion, risk taking and personality profiles, peer leader status and exposure to messaging. These analyses will also investigate subgroup effects, such as whether there are greater effects on help seeking intentions and coping among students with suicidal ideation compared to those without.

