### Procedure

Prior to the commencement of the project in each school, trial liaison managers located in the ACT and NSW will meet with each school to introduce the project to the wider school staff population and to prepare specific clinical protocols within each school. These protocols will detail the processes that will be undertaken if a student reports high levels of suicidality in the trial questionnaires. Student questionnaires will be viewed by the trial liaison managers following their completion to identify ‘at-risk’ respondents. School psychologists, counsellors, or a nominated staff member will be notified of ‘at-risk’ students, and they will follow up with them in accordance with usual school procedures. Students will also be provided with help-seeking contacts (e.g. school psychologist/counsellor or general practitioner) and information (e.g. telephone helplines or websites).

Following the development of clinical protocols, schools allocated to the intervention condition will nominate school staff to act as adult advisors for the Sources of Strength program. The selected staff will be provided with training in the Sources of Strength program, and will undertake the nomination process for peer leaders. At the commencement of the study, all consenting students in participating schools (both intervention and control) will be invited to complete a pre-intervention questionnaire. Questionnaire completion will be co-ordinated by the trial liaison managers to ensure standardisation and student privacy. Questionnaires will be delivered during school time and will be completed online or via paper and pencil, depending on school preference and resourcing. The assessments will take approximately 30 to 40 minutes to complete and have been designed to reduce participant burden. All data will be securely stored at The Australian National University, with access to the data restricted to trial personnel and investigators.

Following completion of the pre-intervention questionnaire, students in intervention condition schools who have been nominated as peer leaders will undertake the Sources of Strength peer-leadership training (4–6 hours over 1 day). Following this training, the peer leaders will meet with the adult advisors in their school on a fortnightly basis to plan and undertake 3 months of whole-school messaging. Students in the wait-list control condition schools will undertake usual school activities during this period.

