### Assessments

Table 1 presents the scales that will be administered at each measurement occasion in the Australian Sources of Strength trial. It is noted that the measures included are relevant to different, sometimes multiple, study aims. All measures have previously been evaluated with adolescent samples and have good psychometric properties.

**Table 1 Tab1:** Questionnaire scales for the Sources of Strength trial

	Pre-intervention	Post-intervention	6-month follow-up	18-month follow-up	No. of items
Demographics	✓	✓	✓	✓	6
Help-seeking Measures					
Adapted GHSQ	✓	✓	✓	✓	11
Adapted AHSQ	✓	✓	✓	✓	12
Help-seeking from adults	✓	✓	✓	✓	4
Help-seeking from adults at school	✓	✓	✓	✓	4
Reject codes of silence	✓	✓	✓	✓	4
Adult help for suicidal youth	✓	✓	✓	✓	4
Trusted adults at school	✓	✓	✓	✓	4
Referral of distressed peers	✓	✓	✓	✓	5
Positive coping					
SWEMWBS	✓	✓	✓	✓	7
SoS coping	✓	✓	✓	✓	8
Social support	✓	✓	✓	✓	15
Mastery	✓	✓	✓	✓	7
Suicidality					
YRBS	✓		✓	✓	4
SIDAS	✓	✓	✓	✓	5
Suicide risk models					
INQ	✓	✓	✓	✓	15
ACSS	✓	✓	✓	✓	7
Entrapment	✓	✓	✓	✓	4
Risk and protective factors					
Self-harm	✓	✓	✓	✓	3
SOSS	✓	✓	✓	✓	16
LOSS	✓				12
DQ5	✓	✓	✓	✓	5
MDI	✓	✓	✓	✓	13
SCARED-GAD	✓	✓	✓	✓	9
Bullying	✓	✓	✓	✓	3
Peer integration at school	✓	✓	✓	✓	4
School identification	✓				2
SURPS-23	✓				23
RTSHIA (RT)	✓	✓	✓	✓	8
Social network variables					
No. of friends	✓	✓	✓	✓	3
No. of trusted adults	✓	✓	✓	✓	2
Naming trusted adults	✓	✓	✓	✓	9
Naming close friends	✓	✓	✓	✓	21
Intervention engagement					
Intervention reach^a^		✓		✓	11
Fidelity questions^b^		✓		✓	6

*ACCS* Acquired Capability for Suicide Scale, *AHSQ* Actual Help-Seeking Questionnaire, *DQ5* Distress Questionnaire-5, *GHSQ* General Help-Seeking Questionnaire, *INQ* Interpersonal Needs Questionnaire, *LOSS* Literacy of Suicide Scale, *MDI* Major Depression Inventory, *RTSHIA* (*RT*) Risk Taking and Self-Harm Inventory for Adolescents – Risk-Taking Scale, *SCARED*-*GAD* Screen for Child Anxiety Related Emotional Disorders, *SIDAS* Suicidal Ideation Attributes Scale, *SOSS* Stigma of Suicide Scale, *SoS* Sources of Strength, *SURPS*-*23* Substance Use Risk Profile Scale, *SWEMWBS* The Short Warwick-Edinburgh Mental Well-being Scale, *YRBS* Youth Risk Behaviour Survey

^a^Only students in intervention schools respond to these questions

^b^Only peer leaders in intervention schools respond to these questions

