### Risk and protective factors

A range of putative risk and protective factors will also be measured to be explored as mediators or moderators of intervention effects and for inclusion in models of suicide risk. The factors explored will include self-harm, suicide stigma, suicide literacy, general psychological distress, depressive and anxiety symptoms, bullying, school social inclusion, personality, and risk taking behaviour.

*Self*-*harm* will be measured using three items (yes/no) that assesses the presence of self-injury, whether the intention of the self-injury was to experience pain or suffering and whether the intention of the self-injury was to die.

Suicide stigma will be investigated using the *Stigma of Suicide Scale* (SOSS) [37]. The SOSS contains 16 one or two-word descriptors of people who die by suicide and respondents are asked to rate their level of agreement with each item on a five-point scale ranging from ‘strongly disagree’ to ‘strongly agree’. Higher scores on this scale are suggestive of greater suicide stigma. The *Literacy of Stigma Scale* (LOSS) will also be administered [38] to assess respondent knowledge of the signs and symptoms of suicide, risk factors, and prevention and treatment options. The LOSS consists of 12 items on a ‘true/false/don’t know’ scale. Higher scores are reflective of greater suicide literacy.

General psychological distress will be assessed with the newly developed *Distress Questionnaire Scale* - *5* (DQ5) [39]. This scale contains five items rated on a five-point scale from 1 (never) to 5 (always), with total scores ranging from 5–25. The screener has been shown to be accurate in detecting a range of common mental health problems in community-based settings.

Depressive symptoms will be measured by the *Major Depression Inventory* (MDI) [40]. This scale consists of 12 items (10 questions with 2 sub-items) that cover the ICD-10 and DSM-IV symptoms of depression. These items are rated on a six-point scale from 0 (all the time) to 5 (at no time) with total scale score ranging from of 0 to 50. Higher scores indicate the presence of more depressive symptoms.

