### Statistical analysis

Analyses of continuous measures will be undertaken on an intent-to-treat basis, including all participants randomised regardless of treatment actually received or withdrawal from the study. Mixed-model repeated-measures analyses will be used because of the ability of this approach to include participants with missing data without using biased techniques, such as last observation carried forward [47]. In addition, by incorporating appropriate random effects for schools, this approach can accommodate and assess the magnitude and significance of clustering effects. The primary aim will be evaluated by a contrast examining change in help seeking intentions from pre-intervention to post-intervention in the Sources of Strength condition compared to that in the wait-list control condition. For suicide attempts and other dichotomous outcomes, a comparable binary mixed modelling approach [48] will be used. Differences in relative risk for incidence of suicide attempt from baseline to the 6- and 18-month follow-ups will be assessed. Mediators of intervention outcome including suicidal ideation, depressive symptoms and exposure to school-based messaging will be explored using interaction terms in mixed effects models and using latent class analyses [49]. Models of suicide risk will be developed using regression analyses and structural equation models, testing the Interpersonal Theory of Suicidal Behavior framework and examining the role of additional psychosocial and demographic risk factors. Social network factors will be assessed in a subset of two schools (one control and one intervention), evaluating up to seven connections per student at pre- and post-intervention, to estimate a range of network indices of density, reciprocity, clustering and individual centrality. Change in social network characteristics as a function of intervention condition will be tested. During the messaging phase, engagement with social media messages posted by peer leaders at the intervention schools will be analysed by categorising posts and assessing the types of messaging that best engage students by measuring reach through likes, shares, and comments. This sub-study measures ‘digital footprint’ behaviour, and thus complements the self-report measures of connectivity.

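### The stated method for mediators (interaction terms, latent classes) tests moderation or groups students; exposure and peer-leader status allow only a non-randomised analysis within the intervention arm

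*Protocol article*

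**What the plan says.** The method is given in one sentence of the Statistical analysis section: "Mediators of intervention outcome including suicidal ideation, depressive symptoms and exposure to school-based messaging will be explored using interaction terms in mixed effects models". The sentence closes by naming latent class analyses as a second method. No path model or indirect effect is named for these variables. Structural equation models appear in the next sentence, but only for the models of suicide risk.

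The aim being served is in Subsidiary aims. Predictors and mediators "of intervention effects and intervention engagement will also be explored", and the list of candidates includes "peer leader status and exposure to messaging". The same aim then poses a subgroup question: whether effects are larger in students with suicidal ideation than in those without. The section on Risk and protective factors treats mediators and moderators as two different roles.

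On measurement, footnote a to Table 1 says of the reach items: "Only students in intervention schools respond to these questions". They are asked at post-intervention and at 18 months. The Recruitment and Procedure sections place peer leaders in intervention schools only, and control schools are offered the program after all questionnaires are complete.

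For the Major Depression Inventory (MDI), Risk and protective factors says: "These items are rated on a six-point scale from 0 (all the time) to 5 (at no time"), with a total of 0 to 50, and then that a higher score means more depressive symptoms.

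**The concern.** A mediator lies on the path from condition to outcome. The question is how much of the effect runs through it. A moderator is a characteristic across which the effect differs. The article names a method for the second question and attaches it to the first. If the sentence is followed as written, a subgroup difference could be reported as a mechanism, and a real mechanism could be dismissed because an interaction was not significant.

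Exposure and peer-leader status raise a further difficulty. Both vary only among intervention students, so neither can interact with condition, and any association with outcome compares students who were not randomised to their level of exposure or role.

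The depression score is one of the named variables. If its direction is built wrongly, a subgroup result would be read the wrong way round.

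**Working it through.** The plan gives no figure for these analyses. The only number used from it is the design: 16 schools averaging 300 students, 2,400 per condition. That target reproduces: 145 per arm for an effect of 0.33 (80% power, two-sided 0.05, change score with r = 0.5, so variance factor 2(1 − 0.5) = 1). Then 145 × [1 + 299 × 0.04] = 145 × 12.96 = 1,879, and 1,879 / 0.8 = 2,349, against 2,400 stated. The point does not depend on it.

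**Step 1. Can condition interact with the variable?** For 16 × 300 students, take the model with columns 1, condition, X and condition × X, and find its rank.

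| X | Control students | Columns | Rank |
|---|---|---|---|
| Exposure or peer-leader status | coded 0 | 4 | 3 |
| The same, with time and its interactions | coded 0 | 8 | 6 |
| Exposure or peer-leader status | left missing | 4 | 2 |
| Baseline ideation | measured | 4 | 4 |
| Baseline ideation, with time and its interactions | measured | 8 | 8 |

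With controls coded 0, condition × X equals X, so the product adds nothing. Condition and X can still be fitted together, but the slope on X then comes entirely from intervention students. With controls missing, condition is constant. For baseline ideation, and for any variable measured in both arms such as depressive symptoms, the interaction model can be fitted.

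**Step 2. Where the model can be fitted, which question does it answer?** Two situations were simulated, 400 runs each, with 16 schools of 300, ICC 0.04 and school effects removed by within-school centring. The effects are assumptions, since the article gives none.

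- Pure mediation: condition shifts the mediator by −0.5 and the mediator acts on the outcome with slope −0.66. The indirect effect is (−0.5) × (−0.66) = 0.33, with no interaction. The condition × mediator test rejected in 3.3% of runs, near the nominal 5% (simulation error √(0.05 × 0.95 / 400) = 0.011).
- Pure moderation: a direct effect of 0.33 and an interaction of 0.2, with condition not affecting the variable. The mean estimated indirect effect was 0.00. The test rejected in 100% of runs.

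The test therefore had no power for mediation and responded fully to moderation.

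**Step 3. Are data available for a proper mediation model?** Table 1 shows the ideation scale (SIDAS), the MDI and the help-seeking intentions measure (GHSQ) at all four occasions, with no restriction by arm. The yes/no suicidality items (YRBS) are not asked at post-intervention, so SIDAS is the usable ideation mediator at that point.

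**Step 4. Direction of the MDI.** On the printed anchors, a student with every symptom all the time scores 10 × 0 = 0, and one with none scores 10 × 5 = 50. That is the reverse of the stated direction. Reverse coding is mentioned for the mastery and interpersonal-needs scales, but not here.

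**The case against.** The article never says that condition would interact with exposure. It says only interaction terms in mixed models, and in a repeated-measures plan that may mean exposure by time within the intervention arm. The aim also covers engagement, which is naturally a within-arm question. This stands. A reader might infer that the exposure models cannot be fitted at all; the document does not support that. What cannot be identified is an interaction with condition.

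Peer-leader status is not in the analysis sentence. It appears only in the Subsidiary aims list, with no method attached. A reader might also say that both variables are missing for half the sample, about 2,400 of 4,800. That is too strong: no control student is a peer leader, so the value is zero by design, and program exposure can be coded zero in the same way.

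An interaction of condition with mediator can be one term in a mediation model, the source cited for latent classes is not at hand, and an analysis plan may hold the full specification. This is fair, and the point is not that detail is missing. It is that the method the article does state does not match the question it is stated for, and that its own text runs a subgroup question and a mediation question together.

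On the MDI, the intended direction is explicit, so the anchors may simply be a slip of wording. A reader might infer that every depression result would change sign. That assumes the stated direction is ignored. Even then, only signs would change, not sizes or tests, and an indirect effect through the score would be unaffected, because both its paths reverse: (−a) × (−b) = ab.

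**Conclusion.** The concern holds in limited form. For ideation and depressive symptoms, the interaction model can be fitted but answers moderation, and latent class analysis as named gives no indirect effect. For exposure and peer-leader status, an interaction with condition is not identifiable under either coding; a within-arm analysis is possible and legitimate, but it is observational and does not show mediation of the randomised effect. The rank result follows from the design alone. The simulation percentages rest on assumed effects and on an interaction used alone.

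The MDI contradiction is real but separate, and is a matter of reconciling the text.

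The consequence is modest: these analyses are subsidiary and exploratory, and the primary contrast, the secondary outcomes and the sample size are untouched. What is at risk is the interpretation of later reports on how the program works.

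**What to change.** 1. Call the interaction analyses of baseline ideation and baseline depressive symptoms moderator analyses.
2. For mediation, specify a school-clustered indirect-effect model with mediators measured after baseline in both arms. One workable choice is the post-intervention mediator (SIDAS or MDI) and 6-month help-seeking intentions, adjusted for the baseline of both, with an interval for the indirect effect that respects the clustering (only eight schools per arm). State that the path from mediator to outcome is not randomised and assumes no unmeasured confounding.
3. Restrict exposure and peer-leader analyses to the intervention arm and label them observational dose-response or engagement analyses.
4. Reconcile the printed MDI anchors with the stated score direction, and confirm which coding the questionnaire and scoring program use.

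The cost is analysis wording and one additional model. No participants or questionnaire items are needed. Asking the 11 reach items in control schools as well would give a measure of contamination, but it lengthens a 30 to 40 minute questionnaire in a trial already recruiting. It is optional, and the fix does not depend on it.

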### Randomisation

Each participating school (cluster) will be randomised to the intervention or wait-list control condition. Cluster randomisation will be undertaken for administrative convenience, to avoid contamination of the wait-list control condition and for the ecological validity of providing the intervention at the school level. School randomisation will be carried out by a statistician not involved in the day-to-day conduct of the trial according to ICH Guidelines [18]. As whole schools will be allocated to a single condition (cluster design), a minimisation approach [19, 20] will be used to ensure balance across conditions on the basis of school location (ACT/NSW), school type (private/public), number of students, and sex ratio.

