### Social network variables

A number of measures, developed specifically for this trial, will also be included to measure social networks and Sources of Strength intervention effects through these networks. These include the following:*Number of friends* – Assessing the number of close friends at school and online (three items)*Number of trusted adults* – Assessing the number of trusted adults at school and outside of school (two items)*Naming trusted adults* – Listing the names of seven adults whom students would ask for help for a suicidal friend*Naming close friends* – A sub-set of students will be invited to list up to seven of their closest friends, how likely they are to seek help from these friends, and how much they are influenced by them, which will be included in a social network analysis.

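### The social-network analysis plans a test of condition with one school per arm, which cannot separate the program from the school, and the aims describe a different set of schools

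*Protocol article*

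**What the plan says.** All references are to the Protocol article.

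- **Randomisation:** "Each participating school (cluster) will be randomised to the intervention or wait-list control condition".
- **Statistical analysis**, on the network sample: "Social network factors will be assessed in a subset of two schools (one control and one intervention"). On what is measured: "evaluating up to seven connections per student at pre- and post-intervention, to estimate a range of network indices of density, reciprocity, clustering and individual centrality". On the inference: "Change in social network characteristics as a function of intervention condition will be tested".
- **Subsidiary aims** describes the same work as an "analysis in a subset of intervention schools to determine whether peer leader messaging increases the density of positive social ties across students". No control school is mentioned there.
- **Social network variables** says only "A sub-set of students will be invited to list up to seven of their closest friends", without naming the arm or the school.

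No section limits the two-school comparison to description or says how school and condition would be separated. The publication plan at the end of Statistical analysis foresees a separate paper for the network analyses.

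**The concern.** The plan handles clustering elsewhere by a design effect in the sample size and by random effects for schools in the models. Neither device is available when each arm contains a single school. Whatever else changed in one of the two schools between the pre- and post-intervention surveys, such as staffing, a critical incident or a change in year-group composition, would appear in the same contrast as the program.

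Subsidiary aims asks a causal question, namely whether messaging raises the density of positive ties. A significant result from the planned test could therefore be published as an effect of the program when the design cannot support that.

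The two descriptions of the sample add a second problem. On one reading there is a control network; on the other there is none. The two imply different analyses.

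**Working it through.** **1. The plan's own figures (Sample size and power calculations).** Inputs: effect size 0.33, power 0.80, two-sided α 0.05, baseline–endpoint correlation r = 0.5, ICC 0.04, 300 students per school, 20% attrition.

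- Design effect = 1 + (300 − 1) × 0.04 = 12.96, as stated.
- A change score has variance factor 2(1 − r) = 1, so n = 145 per arm before clustering. Then 145 × 12.96 = 1,879, and 1,879 / 0.8 = 2,349 per arm, or 4,698 in total. This is within 3% of the stated 2,400 and 4,800.

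The main calculation thus applies a clustering correction even after using the baseline correlation. The document gives no sample size or power for the network sub-study.

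**2. What one school per arm allows.**

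- Between-school degrees of freedom = 2 schools − 2 condition means = 0. With all 16 schools it would be 16 − 2 = 14.
- Under simple equal allocation of k schools per arm, the smallest two-sided randomisation p-value is 2 / C(2k, k). For k = 1 this is 2 / 2 = 1.0. (The trial uses minimisation, so this is only a yardstick.)
- Whole-network density gives one value per school per wave, hence one change score per arm.

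None of these results depends on the ICC.

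**3. Illustrative error rate if students were treated as independent.** Actual type I error = 2 × [1 − Φ(1.96 / √DE)], with DE = 1 + (m − 1) × ICC and m = 300 × 0.8 = 240.

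The planned test is of change, so the relevant ICC is that of change scores. Assume unit variance at each wave, a school variance of 0.04 at each wave, and a pre–post correlation ρ of school effects:

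- between-school variance of change = 2 × 0.04 × (1 − ρ) = 0.08 × (1 − ρ)
- total variance of change = 2 × (1 − 0.5) = 1
- ICC of change = 0.08 × (1 − ρ)

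The document does not give ρ.

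| ICC used | Basis | DE (m = 240) | Type I error |
|---|---|---|---|
| 0.004 | assumed ρ = 0.95 | 1.956 | 0.16 |
| 0.008 | assumed ρ = 0.90 | 2.912 | 0.25 |
| 0.02 | lower ICC cited | 5.78 | 0.41 |
| 0.04 | ICC used for sample size (also ρ = 0.5) | 10.56 | 0.55 |

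At m = 300 the last two rows become 0.46 (DE 6.98) and 0.59 (DE 12.96).

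**4. The two descriptions of the sample.** Statistical analysis has one control and one intervention school. Subsidiary aims has a subset of intervention schools. Both cannot be right.

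**The case against.** The strongest reply is that the analysis is of change, so stable differences between the two schools cancel. That is correct, and it matters for size. A reader might infer that the true type I error is about 55%, but the documents do not support this as a fact:

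- The ICCs of 0.02 and 0.04 were cited for the main-trial sample size; none is given for any network index or for change in one.
- If school effects are highly stable over time, the change-score ICC is much smaller.
- The figure of 240 supposes that every retained student in the school takes part, whereas only a subset of students is invited to name friends.
- The document does not say that students will be analysed as independent, and an article may leave the model to a fuller plan.

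What does not survive is the idea that differencing rescues the test. It leaves school-specific change in place, and with one school per arm that change is inseparable from condition under any model.

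A reader might also infer that no standard error can be formed for density or reciprocity. That goes too far. Network models and resampling give standard errors conditional on the observed networks, and local clustering and individual centrality are student-level indices. Such standard errors describe these two schools; they do not separate school from condition.

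Finally, this is a subsidiary aim. That is true and it limits the weight of the point, but the text still states a test by condition.

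**Conclusion.** The point holds on two grounds. First, the planned test of condition has 0 between-school degrees of freedom. Any p-value for condition would be conditional on these two schools and would not be a valid test of the program. This follows from the school being the randomised unit and needs no assumption about the ICC. Second, Subsidiary aims and Statistical analysis name different schools.

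The size of the error is illustrative only: roughly 16–25% under an assumed change-score ICC of 0.004–0.008, and 41–55% if the main-trial ICCs applied to change, in each case with 240 students analysed as independent. All of these are well above the nominal 5%, but none is an estimate for this sub-study.

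It would be wrong to infer that the network data are worthless or that the trial's main conclusions are at risk. Within-school questions can still be studied, and the primary outcome, the secondary aims and the sample size are untouched.

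**What to change.** - In Statistical analysis, replace the test of change by condition with a descriptive report of the network indices in each school at each wave, with no p-value for condition and no causal wording.
- Keep within-school network questions, such as the position of isolated students, and label them as applying to the schools studied.
- If a between-arm test of connectedness is wanted, use number of friends, number of trusted adults and naming trusted adults. Table 1 schedules these at every wave, and neither it nor Social network variables restricts them to certain schools. Analyse them in the school-clustered mixed model across all 16 schools (14 degrees of freedom at school level). State that these items do not measure density or reciprocity of student ties, so they answer a related but narrower question.
- Make Subsidiary aims and Statistical analysis name the same schools, and align Social network variables with them.

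The cost is rewording plus a re-targeted analysis of items already planned. Recruitment was still under way when the article was written, so no new data collection is needed. A genuine between-arm test of network density would instead need network data from several schools per arm, which is a larger change and is not required to correct the text.
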